**4.5 Sample Size Calculation**

The sample size required for each experimental group was calculated based on the variability of results from the study by Chang et al. (2014), which evaluated the effects of PBM with a laser on functional recovery of wrist and hand fractures using the Quick DASH questionnaire. Using the power/sample size calculator developed by the University of British Columbia (available at <https://www.stat.ubc.ca/~rollin/stats/ssize/n2.html>), the required sample size was determined to be 42 participants, with 21 per group. Calculations were based on a significance level of 0.05, 90% power, and a 15% loss rate, considering the highest obtained value.

**4.6 Group Composition**

Participants will be divided into two groups:

- **PBM Group**: Participants will receive active PBM administered at home, combined with conventional therapeutic treatment. The equipment, dosimetry parameters, and PBM application frequency are described in item 4.10.
- **Control Group**: Participants will receive placebo PBM administered at home, combined with conventional therapeutic treatment. The equipment description for placebo application is detailed in item 4.10.

**4.7 Randomization and Allocation Concealment**

The sequence generation and envelope preparation will be conducted by a researcher not involved in the study.

Participants will be randomly assigned to the two experimental groups using a random sequence generator (<https://www.randomizer.org/tutorial/>), with the option for block randomization of six participants, forming seven blocks. Opaque envelopes will be numbered sequentially, each containing a sheet with the corresponding experimental group based on the generated order. The envelopes will be sealed and stored in numerical order in a secure plastic container.

Participants meeting all previously described eligibility criteria will be evaluated by four surgeons and included in the study. All participants will undergo the same surgical protocol. The allocation envelope will be opened 24 hours after the surgical procedure when the PBM device is delivered. The device delivery will be performed by the medical resident researcher, who will be aware of the allocations.

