**São Paulo, SP**

**2023**

**ABSTRACT**

Among the various complications of the postoperative evolution of fractures of the proximal humerus (FUP) are pain and joint stiffness, generating significant functional limitation in the affected limb. Physical therapy is the standard treatment for both surgical and non-surgical cases. Studies have shown positive effects of photobiomodulation (PBM) on repair and regeneration of fractures, as well as on analgesia and functional improvement. However, they suggest standardization and additional evidence. This randomized controlled double-blind clinical study will aim to evaluate the effects of PBM on the functional recovery of participants with FUP surgically treated with special locking plates. The 42 participants will be randomized (1:1) into 2 groups, the Control group (standardized physiotherapy treatment associated with simulated PBM) and the PBM group (standardized physiotherapy treatment associated with active PBM). The PBM will be applied by the participant at home every day, for 10 minutes, using a device containing 318 LEDs light emitting diodes, 159 LEDs of 660 nm (28.5 mW; 12 J/cm2; 17 J per LED) and 159 850 nm LEDs (23 mW; 10 J/cm2; 14 J per LED). The PBM and physiotherapy sessions (30 minutes, 2 times a week) will be held for 12 weeks. Participants will not be aware of their allocation and will be assessed at 24h, 1, 2, 4, 8 and 12 weeks after the surgical procedure by 4 examiners who are also blinded to each participant's allocation. The main outcome, evaluated in all experimental periods, will be the recovery of shoulder function using the Quick-DASH functional scale. Secondary outcomes will be assessments of range of motion of the shoulder using a digital goniometer, quality of life using the SF-6 questionnaire and the occurrence of adverse effects in all experimental periods. Spontaneous pain, pressure pain (dolorimeter), nocturnal pain and the use of analgesics will be evaluated at 1, 2, 4, 8 and 12 weeks; consolidation of fractures at 4, 8 and 12 weeks through radiographic examinations; and muscle strength by progressive weight bearing at 8 and 12 weeks. In addition to punctual evaluations, each participant will be monitored daily through telephone contact. The collected data will be stored, organized in a repository and the appropriate statistical tests will be applied for each specific analysis. In all tests, a significance level of 5% will be adopted.

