**4.1 Study Location and Sample Selection**

The surgical procedures, outpatient follow-ups, and physiotherapy will be conducted at the Orthopedics and Traumatology Clinic of [name] Netto Hospital (HMACN), part of the Municipal Health Department of São Paulo, Brazil, between April 2024 and December 2025.

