**4.2 Research Team**

The research team will consist of:

- **1 Researcher**: Responsible for preparing the randomization process and envelopes to ensure allocation confidentiality. This researcher will not participate in any evaluations.
- **1 Researcher (medical resident)**: Responsible for retrieving the allocation envelope upon participant enrollment, delivering the appropriate PBM equipment (active or placebo), and providing instructions for home use.
- **4 Surgeons with experience in proximal humerus fractures (PHF)**: Responsible for all surgical procedures and participant eligibility evaluations.
- **4 Blinded Orthopedic Medical Examiners**: Responsible for all evaluations, from postoperative assessments to outpatient follow-ups, while remaining blinded to the experimental group of each participant.
- **1 Principal Researcher**: An orthopedic physician aware of group allocations during the data collection phase and responsible for coordinating data collection. This researcher will not participate in any evaluations and will oversee data interpretation.
- **1 Physiotherapist (blinded to the experimental group)**: Responsible for accompanying participants during all sessions.
- **3 Medical Residents (blinded to the experimental group)**: Responsible for daily contact with participants to monitor PBM device usage, provide guidance, and address any questions.

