**4.12 Photobiomodulation (PBM) Application**

PBM will be administered using LED devices in the form of a shoulder brace. Applications will commence 24 hours after surgery and will continue daily throughout the experimental period. Participants will perform the applications at home, receiving guidance on how to wear and operate the equipment upon hospital discharge, along with written instructions (Appendix 9). Each application will last 10 minutes.

The shoulder brace, manufactured by Cosmedical (Mauá, SP, Brazil), contains 159 red LEDs and 159 infrared LEDs arranged alternately. The area corresponding to the fixation plate, with a 2 cm safety margin added along its entire length, will not be irradiated (LEDs will not be placed there) to avoid potential heating of the plate from energy absorption.

Participants allocated to the control group will receive a device identical to the active one. However, only the activation plug light and sound will turn on when the button is pressed, leaving the internal LEDs deactivated

[figure not shown]

Figure . Design (A) and model (B) of the shoulder brace for PBM application.

Literature reports on the use of PBM after bone fractures indicate the use of red and infrared light sources with varying dosimetric parameters (Table 1), with radiant exposures ranging from 3 to 16 J/cm². The study by Chang et al. (2014), which served as the basis for the sample size calculation in this project, demonstrated positive effects of PBM on functional recovery of wrist and hand fractures using the Quick DASH questionnaire, with a radiant exposure of 9.7 J/cm². Accordingly, this project adopted radiant exposures of 10 J/cm² and 12 J/cm²

| **Wavelength (nm)** | **Power (mW)** | **Irradiance (mW/cm²)** | **Time (sec)** | **Radiant Exposure (J/cm²)** | **Radiant Energy (J) per Point** | **Number of Applications** | **Application Points** | **Results** | **Authors** |
| --- | --- | --- | --- | --- | --- | --- | --- | --- | --- |
| 830 | - | - | - | 8 and 16 | - | Once per day | Sensitive points | Earlier symptom resolution and ambulation | Chauhan & Sarin (2005) |
| 830 | 60 (average power) | 16.2 ± 1 | 600 | 9.7 | 2.5 | 10 | 1 | Pain relief and improved consolidation in conservative wrist fracture treatment | Chang et al. (2014) |
| 808 & 650 | 300 & 100 | 30 ± 20 | 20 ± 30 | 6 ± 3 | 6 ± 3 | 1 | 10 to 12 | Less opioid consumption in tibia fracture treatment | Nesioonpour et al. (2014) |

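### A fixed, published block size of six makes about a quarter of assignments certain in advance to the two staff who know past allocations; undisclosed varying blocks would cut this sharply.

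*Protocol*

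**What the plan says.** Protocol section 4.7 sets out random allocation by an online sequence generator "with the option for block randomization of six participants, forming seven blocks". Assignments are placed in sequentially numbered, opaque, sealed envelopes. The abstract gives the ratio: "The 42 participants will be randomized (1:1) into 2 groups". Section 4.5 gives the total: "the required sample size was determined to be 42 participants, with 21 per group". Section 4.1 names one hospital, and no stratification factor is stated, so there is one list.

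Two people know allocations while the trial runs. Section 4.7 says of the first: "The device delivery will be performed by the medical resident researcher, who will be aware of the allocations". Section 4.2 describes the second, the principal researcher, as "An orthopedic physician aware of group allocations during the data collection phase and responsible for coordinating data collection", and adds that this person takes no part in evaluations.

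Section 4.2 gives eligibility to four surgeons. It describes the examiners, the physiotherapist and the telephone residents as blinded, but does not describe the surgeons either way. Consent follows confirmation of eligibility (section 4.8). The envelope is opened 24 hours after surgery (section 4.7). The exclusion criteria in section 4.4 include complications arising during surgery, and these participants leave the statistical analyses.

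**The concern.** Sealed envelopes hide what is inside the next envelope. They do not hide what follows from the earlier ones when the block size is known and fixed. Once three participants in a block of six have gone to one arm, every remaining place belongs to the other. The block size is printed in the protocol and the envelopes are numbered, so anyone who also knows the earlier allocations in the current block can see when this happens.

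What is at stake is the comparability of the arms. Between consent and envelope opening, a participant can still be dropped for a surgical complication. If a person who can foresee the next assignment influenced who is enrolled or who is dropped, the groups could differ for reasons other than treatment. With 21 per arm, a few such decisions could matter. As written, the protocol relies on the informed staff having no influence, but does not say that they have none.

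**Working it through.** **Inputs.** Block size 6, seven blocks (section 4.7); allocation 1:1 (abstract); 42 participants, 21 per group (section 4.5); one list (section 4.1, no stratification stated).

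**Step 1: the plan's own layout.** 7 × 6 = 42 and 7 × 3 = 21 per arm. This reproduces the stated figures exactly.

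**Step 2: assignments that are certain.** Take an observer who knows the block size, where each block starts and every earlier allocation. An assignment is certain once one arm has used its three places, so the number of certain assignments in a block equals the length of its final run of identical assignments. A block of six has 20 possible orderings:

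| Length of final run | Orderings | Product |
| --- | --- | --- |
| 1 | 12 | 12 |
| 2 | 6 | 12 |
| 3 | 2 | 6 |
| Total | 20 | 30 |

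Mean = 30 / 20 = 1.5 of 6, or 25%. This agrees with the general result for a 1:1 block of size 2m, where the certain share is 1/(m + 1); for m = 3 it is 1/4. Over the trial, 0.25 × 42 = 10.5 assignments.

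**Step 3: best guess.** The same observer, always guessing the arm with more places left, is right on average 4.1 times in 6, or 68.3%, against 50% without any information.

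**Step 4: varying block sizes.** This was checked by simulating 20,000 lists of 42. The observer knows every past assignment and the set of possible sizes, but not the sizes drawn. Sizes are drawn independently with equal probability.

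| Block sizes | Certain | Of 42 | Best guess right | Certain if drawn sizes become known |
| --- | --- | --- | --- | --- |
| 6 only (plan) | 25.0% | 10.5 | 68.3% | 25.0% |
| 4, 6 | 5.6% | 2.4 | 68.9% | 27.4% |
| 2, 4, 6 | 4.0% | 1.7 | 70.0% | 31.3% |
| 4, 6, 8 | 2.3% | 1.0 | 67.7% | 23.6% |

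Varying the sizes removes most of the certainty but leaves average guessing success almost unchanged. The gain also depends on secrecy: once the drawn sizes are known, about a quarter or more is certain again.

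**Step 5: effect on balance.** If independently drawn blocks of 4, 6 and 8 are cut off at 42, the arms are unequal in 27.6% + 0.4% = 28.0% of lists, nearly always 22 v 20. A set constrained to the total avoids this: 4 + 4 + 6 + 6 + 6 + 8 + 8 = 42, with half of each block in each arm, giving 21 and 21.

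**The case against.** The strongest objection is that the people who can predict are not the people who decide. Section 4.2 gives eligibility to the surgeons, the resident acts only once a participant is enrolled, and the principal researcher does no evaluations. The complications that lead to exclusion are specific surgical events, and neither aware person is given a role in judging them. Fixed blocks with numbered, opaque, sealed envelopes are a coherent design, and the layout adds up. All of this stands. It limits the point to a risk that needs information or influence to pass from the aware staff to the surgeons, a route the protocol neither documents nor closes.

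A reader might infer more, in four ways that the material does not support.

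- **That selection bias is shown.** It is not. The 25% describes what an informed observer could know, not what anyone did.
- **That varying block sizes would make prediction impossible.** They would not. About 2% of assignments stay certain with sizes 4, 6 and 8, and best-guess success stays near 68%.
- **That the change is free.** The list must be regenerated, and the exact 21 v 21 split is no longer guaranteed unless the sizes are constrained to total 42.
- **That the sham device adds to the 25%.** In the control device "only the activation plug light and sound will turn on when the button is pressed" while its internal LEDs stay off, so a participant's remark might reveal one assignment. That is a masking question which block size does not settle. One remark gives one allocation, whereas the 25% requires all the earlier ones in the block.

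**Conclusion.** The point holds as a minor design improvement. The published block of six makes on average 25% of assignments (about 10.5 of 42) certain in advance to the two allocation-aware team members. This assumes that they know every earlier allocation in the current block and where the block starts. The resident sees each opened allocation and can read block starts from the envelope numbers. For the principal researcher, it assumes that allocations become known as they accrue and not only later.

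Bias from this is possible, because the surgeons are not stated to be blinded and exclusion for surgical complications can precede envelope opening. It is not demonstrated. Undisclosed varying blocks would cut the certain share to about 2% (about 1 of 42). That figure is for sizes drawn independently from 4, 6 and 8 and kept secret. The benefit lies in certainty alone, not in average guessing success.

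**What to change.** In section 4.7, replace the seven blocks of six with randomly ordered blocks of varying size that total 42; a shuffled set of 4, 4, 6, 6, 6, 8 and 8 is one example. Leave the sizes and the make-up of the set out of the protocol, and let only the list preparer know them. Reconcile who that person is: section 4.2 lists the preparer within the research team, while section 4.7 describes someone not involved in the study.

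Add a sentence stating that staff who know allocations take no part in eligibility decisions or in exclusions after surgery. Block sizes alone do not cover that route.

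If enrolment has begun, apply the change from the next complete block, with new sizes that sum to the places left, so that no block in progress is cut.

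The cost is one regenerated list, new envelopes and a short text change. The arms may differ slightly, usually 22 v 20, if the list is not constrained to 42 or if recruitment stops in the middle of a block.

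### The resident who gives the first face-to-face teaching in home use knows the participant's arm; numbering the devices would avoid this

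*Protocol*

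**What the plan says.** Section 4.7 places sealed, numbered, opaque envelopes in order, "each containing a sheet with the corresponding experimental group based on the generated order". On timing it states: "The allocation envelope will be opened 24 hours after the surgical procedure when the PBM device is delivered". On the person it states: "The device delivery will be performed by the medical resident researcher, who will be aware of the allocations".

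Section 4.2 assigns one medical resident to retrieve the envelope, and adds "delivering the appropriate PBM equipment (active or placebo), and providing instructions for home use" to that resident's tasks. Section 4.12 has participants apply PBM at home, "receiving guidance on how to wear and operate the equipment upon hospital discharge, along with written instructions (Appendix 9").

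On the devices, section 4.12 says: "Participants allocated to the control group will receive a device identical to the active one". It then qualifies this for the sham: "only the activation plug light and sound will turn on when the button is pressed, leaving the internal LEDs deactivated". The brace "contains 159 red LEDs and 159 infrared LEDs arranged alternately".

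Section 4 calls the trial double-blind. The abstract and section 4.2 keep participants, the four examiners, the physiotherapist and the three telephone residents unaware of allocation. Section 4.13 has the telephone residents repeat the instructions in a first video call and then ring every day, partly to support adherence. The protocol describes no step in which devices are coded and dispensed by number.

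**The concern.** The treatment is self-applied daily for 12 weeks, and the primary outcome is a questionnaire that participants complete about their own function. Pain is also self-reported. The teaching at hand-over is the first occasion on which a participant learns to fit the brace, hears how important daily use is and forms an expectation of benefit. If the teacher knows the arm, the emphasis or encouragement can differ between arms without anyone intending it. A difference in QuickDASH that arose this way could not be separated in the analysis from an effect of PBM, and blinded examiners do not close the route, because the participant supplies the answers.

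The protocol blinds the other staff who treat, assess or telephone participants after surgery. The device trainer is the exception, and the exception looks unnecessary: an unlit brace can be handed over by number.

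**Working it through.** **1. Is the trainer unblinded by the plan's own text?**

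| Step | Source | Content |
|---|---|---|
| Envelope sheet | 4.7 | Names the experimental group |
| Envelope retrieved by | 4.2 | The medical resident researcher |
| Device delivered by | 4.7 | The same resident, stated to know the allocations |
| Home-use instructions given by | 4.2 | The same resident |
| Primary outcome | 3.1, with the DASH description in section 1 | QuickDASH, short form of a self-administered questionnaire |

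Section 4.7 does not say in words who opens the envelope. This does not matter, since it says that the person delivering the device knows the allocations. The answer is yes.

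**2. Does hand-over require that knowledge?** Someone must know which braces are active. The researcher who prepares the sequence and envelopes already does, and takes no part in evaluations (4.2). The resident needs only to know which brace belongs to which participant, which a number supplies. One condition applies. The braces are described as identical, but when powered the active one lights 159 LEDs at 660 nm (4.12, Table 2), which is red light, while the sham's LEDs stay off. A number conceals the arm from the trainer only if the participant's own brace is not switched on in front of the trainer.

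**3. What in the plan already limits the effect?** Written instructions (4.12), the blinded video call that repeats positioning and use, and daily blinded calls (4.2, 4.13). The calls begin only after discharge, so they follow the unblinded teaching and do not replace it.

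**4. How sensitive would the test be to a spurious shift?** The protocol states no figure here to reproduce, and section 4.5 gives neither a difference nor an SD. Inputs:
- Evaluable per arm: 21 × (1 − 0.15) = 17.85, taken as 18 (4.5).
- Two-sided test at 5% (level from 4.5; two-sidedness assumed), two-sample t-test with 2 × 18 − 2 = 34 degrees of freedom, critical value 2.032.
- SD of 15 or 20 points, and spurious shifts of 2, 3 or 5 points: all assumed.

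With no true effect, the rejection probability is P(|T| > 2.032), where T is noncentral t with noncentrality λ = (shift/SD) × √(18/2) = 3 × shift/SD.

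| Shift | λ, SD 20 | False-positive rate | λ, SD 15 | False-positive rate |
|---|---|---|---|---|
| 2 | 0.30 | 6.0% | 0.40 | 6.7% |
| 3 | 0.45 | 7.2% | 0.60 | 9.0% |
| 5 | 0.75 | 11.3% | 1.00 | 16.3% |

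The table shows how the error rate would respond to a given bias. It does not estimate the bias.

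**The case against.** The strongest reply is that the unblinded contact is one hand-over with its instruction, followed by about 12 weeks of daily contact with blinded staff, one of whose stated aims is adherence. Participants also have written instructions, and their training is repeated by someone who does not know the arm. This stands as mitigation: it makes a large, lasting shift from the first teaching less plausible, and the upper figures in the table need just such a shift. It does not make the first teaching blinded.

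A second reply is that numbering leaves a visible difference untouched, because the active LEDs light and the sham's do not. This also stands, as a limit on what the fix achieves. Participants might notice the difference at each use, and nothing proposed here addresses that. It is no reason to leave the trainer unblinded as well.

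A third reply is that the resident's knowledge is openly disclosed. That is correct. A reader might infer that the double-blind label is false or that the protocol contradicts itself. The documents do not support this: the protocol applies blinding to participants and examiners, among others, and states plainly that this resident is not blinded. A reader might also infer that the result will be tilted towards PBM. No passage establishes that coaching will differ, or in which direction.

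**Conclusion.** The point holds as an avoidable gap in blinding, of modest weight. By the protocol's own text, the first face-to-face teaching of a self-applied, sham-controlled treatment with a self-reported primary outcome is given by someone who knows the arm. This is a route for bias; it does not show that bias or unblinding of participants will occur.

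The conclusion rests on the text of sections 4.2, 4.7 and 4.12 and needs no numerical assumption. The illustrative range of about 6% to 16% depends wholly on the assumed shifts and SDs. The change is worth making because it is cheap, not because a large distortion has been shown.

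**What to change.** - **Section 4.7:** replace the experimental group on the envelope sheet with a device number unique to each participant. Avoid a shared two-letter code, where one disclosure would reveal every participant's arm. State that the researcher who prepares the sequence labels the active and sham braces and holds the key. Delete the clause saying that the delivering resident knows the allocations.
- **Sections 4.2 and 4.7:** state that the resident hands over the numbered brace without knowing the arm and does not switch on the participant's own brace during teaching. Operation can be taught from the written instructions or with a demonstration brace. An unpowered one shows fitting; a sham one can also show the button, plug light and sound.
- **Section 4.2:** this section also says that the principal researcher knows the allocations during data collection. Reconcile that with the new rule on who may see the key; otherwise the two statements will conflict.

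Cost: labels, a key list, custody of the key during recruitment, relabelling of any re-used devices, and possibly one demonstration brace. The sequence preparer's role widens slightly beyond what 4.2 and 4.7 now describe. No extra visits or participants are needed.

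Limit: this blinds the trainer only. Whether participants can tell lit from unlit LEDs needs its own answer.
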